## Methods: data collection, management, and analysis

### Data collection plan

We are collecting trial data from a variety of sources for measuring health, indoor climate, economic, and behavioral outcomes (Table 2). Our primary outcome — heart rate — is collected monthly by trained field staff using an Omron portable automated sphygmomanometer. We present a complete list of secondary outcomes, including the associated instruments used for data collection in Table 2. Additionally, we are collecting continuous health indicators, including heart rate, sleep, and activity using a Withings Pulse HR or Garmin Vivosmart 5 smartwatch worn by a subset of participants.

We are collecting HbA1C blood samples - an indicator of long-term glucose control as two-panel measurements in the hottest months of 2021 and 2022, respectively, using the HemoCue® HbA1c 501 System. A qualified phlebotomist took 4 ml of whole blood by venipuncture for each participant. The phlebotomist labeled the collection tube with the participant's first and last name, and their household, individual and study identifying codes. Blood samples collected in different villages were stored in a refrigerator, and transfered to the laboratory within 48 h. Our laboratory technicians verified that HbA1c samples matched participants and recorded measurements systematically on examination forms according to protocols supplied by HemoCue®. Blood samples were subsequently disposed of in accordance with the laboratory's biological waste disposal procedure. We removed all identifiable information, except the individual identification code, prior to conducting data analysis.

We are collecting indoor temperature and humidity data using the DS1923-F5 iButton hygrochron temperature and humidity sensors. We are also conducting three independent sub-studies using the cool roof trial infrastructure that will be reported separately. First, we will investigate the effects of cool roofs on mosquito abundance, where light traps and aspirators are deployed during the rainy season to collect mosquito samples from a subset of households. Second, we will investigate the effects of cool roofs on farmer productivity, where GPS devices will record individual movement and remote sensing will provide data on crop harvest yield. Finally, we will investigate the effects of cool roofs on food consumption, psychosocial well-being, and gender-based violence from data collected during monthly home visits.

We are creating a secure SQL relational database hosted at Heidelberg University to unite individual data streams. We will merge data through unique identifying codes for each participant and subsequently clean data to remove duplicates and identify missing and inaccurate values. We will move cleaned data into the master relational database and record data management processes in a logbook. We are cleaning and consolidating data as it streams in from multiple sources.

We will validate objective measurements such as temperature and humidity against self-reported subjective measures such as heat stress index to gauge the thermal comfort of our study participants in control and intervention homes. Table 2 presents the full range of objective and subjective data collected.

### Data management

We are storing data using numeric identifier codes to maintain participant anonymity in a password-protected database that is only used for analysis by the research team. Access to this database is restricted to a minimum number of people, including the principal investigator (PI), co-investigators, biostatisticians, and data scientists. We follow the principles of long-term preservation and open access, described in the 2010 Principles for the Handling of Research Data adopted by the Alliance of German Science Organizations [52]. While no third party is privy to the original data (primary and secondary endpoints, as well as exposure status information), anonymized data will be made available through the website of the institution, which the PI leads [Heidelberg Institute of Global Health (HIGH), Faculty of Medicine and University Hospital, University of Heidelberg] 1 year after study completion. Restrictions to this open-access model will only apply if standard approaches to guarantee anonymity (removal of names and other personal identifiers) cannot guarantee anonymity (i.e. if triangulations of data from several data sources can reveal identities).

While the data will be openly accessible as described above, users must register (on the HIGH website) with a title and a short description of their research projects. Any publications resulting from analyses of the open-access data from this project will acknowledge funding through the German Research Foundation (DFG).

### Statistical analysis

#### Analysis of monthly home visit data

The analysis for our primary outcome, heart rate, will be performed on the principle of intention-to-treat (ITT). We will use generalized linear mixed models (GLMM) to analyze the causal effect of cool roofs on our primary and secondary endpoints. In addition to the base-case estimations, without covariate controls, we will also estimate the intervention effect of cool roofs by adjusting for covariates to boost statistical efficiency. We will adjust for clustering of standard errors at the household level.

To estimate the intervention effect of cool roofs on heart rate, we will report the effect estimates comparing intervention and control arms based on the hypothesis that effects will be greatest during the hottest month of the year (April). We will additionally report effect estimates at monthly intervals of data collection, except for HbA1c (which is measured in two time points), because we hypothesize the intervention effect will vary based on outdoor weather conditions during the trial period; therefore, we will include an interaction term between the intervention and the month of trial. We will perform additional sub-analysis by selected variables where relevant (i.e., by season, gender, age group, time of the day (day/night), and roof type). We will explore the use of different imputation methods for missing values in the covariates. We will conduct sensitivity analysis, including repeating analyses accounting for individuals lost to follow-up. All data analyses will be performed using R software.

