**Fig. 3 Fig3:**
[figure not shown]
Trial design

Our clusters are homes with roofs eligible for the cool roof intervention. Following the recommendation by Imbens et al. [48], we stratified our cRCT (rather than matching or using covariate information) using many small strata. We stratified on two factors: (i) village and (ii) the two types of roofing materials that exist in the study community (mud brick and tin). In each stratum, we randomized the same number of individuals (12, six women and six men) and homes (6) 1:1 to either receive or not receive the cool roof.

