### Timeline

Our trial began on April 20, 2021. The end of COVID-19 restrictions for home visits coincided with the beginning of the rainy season in June 2021. Due to this short window, we could not collect baseline information from participants. Therefore, we conducted an intensive campaign before the rainy season to apply cool roofs on 300 homes between April 23, 2021, and June 4, 2021. Our 30 cool roof applicators traveled across 25 villages, coating 54 homes per week. Each home required no more than 1 week to coat, including the curing time between preparing the roof surface, primer application, first and second coat application. We verified the iButton data loggers, which measure indoor temperature in each home, were collecting data.

After encountering challenges caused by the COVID-19 pandemic, we faced intermittent delays in three key areas during our research project. First, we encountered difficulties maintaining participant retention due to early equipment malfunctions requiring replacement. Second, due to the rapidly changing on-the-ground security concerns, we had to modify participant questionnaires and make the corresponding ethical amendments. Third, ongoing security concerns in Burkina Faso, including the military’s restrictions on fieldworker movement and data collection, posed additional obstacles to our research progress.

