### Sample size

Of the 59 villages in the Nouna HDSS, 25 were randomly selected (or about half of all the villages in the Nouna HDSS area), generating a total of 50 strata. We randomly selected 12 homes in each village with mud brick roofs and 12 with tin roofs. We randomized these homes (*n* = 600) in each category (1:1) to either the intervention (cool roof application) or the control condition (no cool roof application). The distribution of these 600 households across the trial groups was evenly balanced between mud brick and tin roof houses and between the intervention and control groups. Each of the 600 households enrolled in the study included one female and one male participant (*n* = 1200 participants).

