### Power calculations

Prior non-randomized studies indicate that reducing the indoor temperature by 3–4 °C should decrease heart rate by several beats per minute [32, 50, 51]. Because of high uncertainty about the previous findings, their attributability to the climate and context in rural Burkina Faso, and the relatively large number of secondary endpoints, our cRCT is powered conservatively (Table 3). In the baseline power calculation, the minimal detectable heart rate difference between the cool roof intervention and control condition arm is 0.22 beats per minute (Table 3) for 300 homes (in the intent to treat) in both arms, assuming a significance level of 5% and power of 80%. We further assumed that 15% of homes refuse to participate in the trial and 15% of individuals would be lost to follow-up. Our sensitivity analyses showed that these power calculation results are highly robust to changes in intra-cluster correlation, the number of individuals in which the outcomes were measured per home, and the base correlation generated by our stratification (Table 3).

**Table 3 Tab3:** Minimal detectable difference in heart rate — baseline power calculation and sensitivity analyses

No. individuals/baseline correlation	1	2	3
ICC = 0.1			
0	0.28	0.21	0.18
0.1	0.28	0.21	0.18
0.2	0.28	0.20	0.17
ICC = 0.2			
0	0.28	**0.22**	0.19
0.1	0.28	0.22	0.19
0.2	0.28	0.21	0.19
ICC = 0.3			
0	0.28	0.23	0.21
0.1	0.28	0.23	0.20
0.2	0.28	0.22	0.20

The significance level is 0.05

The table shows the minimal detectable differences in heart rate (in beats per minute) for 300 homes in each arm for a range of combinations of values of the intracluster correlation coefficient (ICC), the number of individuals per home, and the baseline correlation generated by our stratification

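### The base-case model leaves out the 50 village-by-roof strata used to randomise homes; the error is conservative, small for heart rate, and could be larger for indoor climate

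*Protocol article*

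**What the plan says.** **Design.** The Trial design section states "we stratified our cRCT (rather than matching or using covariate information) using many small strata" and "We stratified on two factors: (i) village and (ii) the two types of roofing materials". The Sample size section gives the layout: 25 villages by two roof types, "generating a total of 50 strata"; for the homes within these it says "We randomly selected 12 homes in each village with mud brick roofs and 12 with tin roofs"; and "Each of the 600 households enrolled in the study included one female and one male participant". Each stratum therefore has 12 homes, six per arm, and the trial has 600 homes and 1200 people. The section on assignment of intervention says the arms were balanced on village and roof type and calls these two factors covariates.

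**Analysis.** The section on monthly home visit data plans generalized linear mixed models for heart rate and for the other outcomes alike, and sets two versions of them: "In addition to the base-case estimations, without covariate controls, we will also estimate the intervention effect of cool roofs by adjusting for covariates". The stated purpose of the adjusted version is efficiency, but no covariate is named. Household is the only level at which standard errors are clustered. Roof type appears only as a sub-analysis variable. The smartwatch models have individuals nested within households as random terms, and roof type enters only in supplementary interaction models.

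**Power.** Table 3 varies the household ICC, the number of people per home and "the base correlation generated by our stratification" (0, 0.1, 0.2). The bold base-case value of 0.22 is in the correlation 0 row.

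**The concern.** Stratified randomisation takes differences between villages and between mud-brick and tin homes out of the treatment contrast. A model without stratum terms leaves those differences in the residual or household variance, so the reported standard error is larger than the true sampling variability of the estimate. Confidence intervals are then too wide, and tests reject less often than 5% under the null. The precision that a design with many small strata was chosen to provide is not collected in the analysis.

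This depends on one condition: the strata must be prognostic for the outcome. If they are not, nothing is lost. The question matters most for the indoor-climate endpoints, where roof material and location plausibly drive the level. The protocol itself treats roof type as thermally relevant: it sets limits for anomalous environmental readings by roof type.

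**Working it through.** **Inputs.** From the article: 50 strata, 12 homes each (6 per arm), two people per home, ICC 0.2, 80% power, 5% significance (two-sided assumed, as sidedness is not stated), stratification correlation r = 0, 0.1, 0.2. Not given: the heart-rate SD and any between-stratum variance.

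**Step 1: reproduce Table 3.** Without the SD, 0.22 cannot be derived from the stated inputs alone. The table's structure can be recovered. With

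MDD = (1.96 + 0.84) × SD × √[2 × (1 + (m − 1) × ICC) × (1 − r²) / (n × m)]

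and SD = 1, all 27 cells match to two decimals for n of 197.3 to 199.2 homes per arm. Replacing (1 − r²) by (1 − r) matches at most 13 of 27. For the base case (n = 198.3, m = 2, ICC 0.2):

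- r = 0: 2.80 × √(2.4 / 396.6) = 0.218, printed 0.22
- r = 0.1: 0.218 × √0.99 = 0.217, printed 0.22
- r = 0.2: 0.218 × √0.96 = 0.214, printed 0.21

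So r² acts as the share of variance that stratification removes, and the protocol's largest value corresponds to a share of 0.04. The ratios below do not depend on the SD.

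**Step 2: size of the loss.** Let R be the share of home-mean variance lying between strata, and s = √(1 − R). Without stratum terms the reported standard error is too large by 1/s. The effect is fixed where the plan fixes it, at 80% power with no gain from stratification (2.80 unadjusted standard errors). Then:

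- true type I error = 2 × [1 − Φ(1.96 / s)]
- power without stratum terms = Φ(0.84 / s)
- power with stratum terms = Φ(2.80 / s − 1.96)

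| R | SE ratio | True type I error | Power without | Power with | Difference (points) |
|---|---|---|---|---|---|
| 0 (r = 0) | 1.000 | 5.0% | 80.0% | 80.0% | 0 |
| 0.01 (r = 0.1) | 1.005 | 4.9% | 80.1% | 80.4% | 0.3 |
| 0.04 (r = 0.2) | 1.021 | 4.6% | 80.5% | 81.6% | 1.1 |
| 0.10 (assumed) | 1.054 | 3.9% | 81.3% | 84.0% | 2.7 |
| 0.20 (assumed) | 1.118 | 2.8% | 82.7% | 88.0% | 5.3 |
| 0.30 (assumed) | 1.195 | 1.9% | 84.3% | 91.8% | 7.5 |

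The first three rows cover the protocol's own range. The last three are assumptions, offered as a plausible span for indoor-climate endpoints.

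**Step 3: check by simulation.** Home means were simulated in 50 strata of 12 homes, 20,000 runs per setting. For R = 0.04, 0.10, 0.20 and 0.30, the unadjusted standard error was 1.020, 1.053, 1.116 and 1.193 times the stratum-adjusted one. Power was 79.9% versus 80.9%, 81.4% versus 84.0%, 82.5% versus 87.6%, and 84.6% versus 91.7%. At R = 0 it was 80.2% without and 80.1% with stratum terms, so the degrees of freedom spent cost almost nothing even when the strata are uninformative.

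**The case against.** The strongest reply has four parts.

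- **An adjusted estimate is already planned.** Its purpose is efficiency, and village and roof type are natural candidates for it. This stands in part. However, the adjusted estimate is an addition to the base case, its covariates are not named, and the base case is expressly without covariates.
- **This is a condensed article.** The random effects of the home-visit model are not listed, so a village or stratum term is not expressly ruled out. That is fair. But the article does fix what the base case excludes and where clustering is handled, and neither statement brings in the strata.
- **The error is conservative and small for the primary endpoint.** This stands in full on the protocol's own range.
- **Between-stratum variance is unknown.** This also stands. The figures for indoor climate are conditional on an assumed share.

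Some stronger readings are tempting, and the documents do not support them. A reader might infer that the sample size relies on precision from stratification that the analysis then fails to collect. It does not: the base-case 0.22 uses correlation 0, and the 0.1 and 0.2 rows are sensitivity analyses. A reader might also infer that power falls below the planned 80%; for the same reason it does not. Finally, because "we could not collect baseline information from participants", a reader might suspect that the efficiency covariates are measured after coating and affected by it. No adjustment covariates are named, so that remains speculation.

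**Conclusion.** The point holds in a limited form. As described, the base-case analysis does not use the strata within which homes were randomised, and if those strata are prognostic its standard errors are conservative. For heart rate, on the protocol's own range, they are 0 to 2% too wide, at a cost of 0 to about 1 power point. That range rests on reading the stratification correlation through the (1 − r²) factor, which reproduces every cell of Table 3.

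For indoor temperature, humidity and heat index, a between-stratum share of 10 to 30% of home-level variance would make standard errors about 5 to 20% too wide. That share is an assumption; nothing in the documents confirms or bounds it, and a claim of heavy power loss on these secondary endpoints would go beyond the text. The validity of the trial is not threatened. The change is worth making because it matches the analysis to the randomisation at almost no cost.

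**What to change.** State that the base-case home-visit and indoor-climate models include the village-by-roof strata, either as stratum fixed effects or as roof type fixed plus village random. Keep the household-level handling of clustering. Fixed effects cost at most 49 degrees of freedom (50 strata less one) out of about 600 homes; the mixed version costs fewer.

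In the smartwatch models, add roof type as a fixed effect and village as a random effect, not 50 fixed effects. That subset has 152 people, about three per stratum (152 / 50), and the article does not state that it is balanced within strata.

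No new data are needed: village and roof type had to be known for every home before it could be randomised. Table 3 and the sample size need no change on this account.

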#### Analysis of smartwatch data

Raw indoor and outdoor temperature and relative humidity data, collected in 15-min intervals, will be averaged at the hourly level. We will categorize environmental data as anomalies when measurements are two standard deviations beyond the corresponding monthly average values based on roof type (mud brick or tin roof).

We will analyze data from smartwatches on heart rate and sleep. First, for heart rate data, we will exclude duplicate heart rate measurements or those that exceed the age-predicted maximum heart rate as implausible values. We will round and aggregate remaining heart rate measurements to the nearest 1-h interval to align with summarized indoor and outdoor temperature and relative humidity data. To distinguish daytime and nighttime heart rates, we will use median sleep onset and offset to define nighttime from 22:00 to 06:00 h. Measurements will be analyzed if they reach the threshold of at least 1 h during the same day or night, with a minimum of one measurement every 15 min. The 15-min threshold was selected based on previous research [53]. Second, for sleep data, we will calculate sleep duration based on onset and offset time to eliminate errors and minimize outliers. Only overnight sleep periods, where nighttime sleep is defined as having a sleep onset of ≥ 17:00 and a sleep offset of ≤ 13:00, with a 2-h adjustment made to account for earlier bedtimes of the study population, will be included in the analysis. If a participant has multiple sleep observations in a single night, we will aggregate these into one sleep observation by adding the sleep duration values and the duration between the first offset and last onset to the wake time after sleep onset. We will exclude data where multiple sleep observations overlap for a participant. Furthermore, sleep detections with a time difference of fewer than 3 h between sleep onset and sleep offset will be excluded, in line with the manufacturer’s declaration that such detections represent invalid measurements.

We will evaluate the intervention effects of temperature exposure on heart rate and sleep outcomes using generalized additive mixed models, with individuals nested within households as random terms. Natural cubic splines will be used to evaluate non-linear effects. In cases where non-linear effects are not detected, linear terms will be substituted in the final models. We will present effect estimates of daily exposure averages on daytime versus overnight periods when individuals are most likely present in their homes. Furthermore, we will present intervention effects during the hottest month (April), monthly aggregates, and an overall aggregate for the entire study period. Where relevant, models with continuous daily or intraday time series data will include the day of the year and month indicators to account for time trends and seasonality, respectively. We will present supplementary models with an interaction term between the intervention group and roof type to assess variations resulting from the thermal characteristics of household vernacular architecture.

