In contrast to urban, high-income settings, home occupants in low-resource rural settings in lower- and middle-income countries (LMICs) are particularly vulnerable to indoor heat exposure [30, 31]. Case studies sampling few households demonstrated that passive interventions can reduce indoor heat exposure in LMIC settings [32]. Cool roof technologies, such as solar reflective paints, Thermocol insulation, and ModRoof, have been shown to reduce daytime indoor air temperature by approximately 2.5 °C in both urban and rural areas of India [30, 33]. Housing design modifications incorporating screened windows and lightweight, permeable materials, while more resource-intensive, have also proven effective in reducing the indoor temperature by 2.3 °C in rural Tanzania [34]. Though evidence exists linking active and passive interventions to indoor heat exposure, few population-level pragmatic trials (using gold-standard randomized control trial or quasi-experimental methodology) have investigated the effectiveness of home cooling interventions on outcomes including individual health, environmental, behavioral, and economic outcomes — particularly in populations such as the Nouna HDSS.

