## Methods: participants, intervention, and outcomes

### Setting

We are conducting this study in 600 clusters (homes) in Nouna, Burkina Faso. Nouna is a dry orchard savannah in sub-Saharan Africa characterized by a hot, dry summer (March to May) and heavy rainy season (June to September). Maximum temperature can reach above 40 °C, causing this subsistence farming community of 106,611 inhabitants (rural and semi-urban) considerable discomfort in summer months [49] (Table 1). The study location is an established HDSS community that has regularly collected population health data on vital life events (i.e., births, deaths, in/out-migration) since 1992 (Fig. 4).

**Table 1 Tab1:** Temperature profile in Nouna, Burkina Faso

	**Minimum**	**25%**	**50%**	**Mean**	**75%**	**Maximum**
Temperature (°C)						
**Daily minimum**	3.3	21.1	22.8	23.1	25	32.8
**Daily average**	17.2	27.5	29.2	29.6	31.7	37.8
**Daily maximum**	22.8	33.3	36.4	36.1	38.9	43.9

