#### Outcomes

Table 2 shows the primary and secondary endpoints, including the definition, functional form of the variable, and measurement approach. Figure 5 shows the schedule of enrollment, intervention, and assessment. The primary outcome is heart rate; we collect three measurements monthly from every participant during monthly home visits. In addition to the primary outcome, we are collecting data to assess the effects of cool roofs on (i) secondary environmental outcomes, including ambient temperature and humidity (measured using iButton sensors), and (ii) secondary health outcomes, such as blood pressure, body temperature, heat-related outcomes, blood glucose, sleep, cognition, mental health, health facility utilization, economic and productivity outcomes, mosquito count, life satisfaction, gender-based violence and food consumption. We randomly selected 152 participants [intervention, *n* = 76 (38 women, 38 men) versus control, *n* = 76 (38 women, 38 men)] to receive a smartwatch that continuously monitors heart rate, sleep, and activity. Between August 2021 and July 2022, our participants used the Withings Pulse HR smartwatch for data collection. In July 2022, owing to the fragility of the Withings Pulse HR, we replaced these devices with the Garmin Vivosmart 5 smartwatch. Several Withings Pulse HR smartwatches were breaking with participant use in the field, necessitating this replacement.

**Table 2 Tab2:** Primary and secondary endpoints of the cRCT

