**Secondary endpoints**	
**Air temperature**	Definition: Ambient air temperature (in °C) Functional form: Continuous Measurement: DS1923 iButton Hygrochron heat and humidity measurement device
**Relative humidity**	Definition: Ratio of the amount of water vapor present in the air to the greatest amount possible at the same temperature (in %) Functional form: Continuous Measurement: DS1923 iButton Hygrochron heat and humidity measurement device
**Heat index**	Definition: Index that combines air temperature and relative humidity (using the formulae endorsed by the US National Oceanic and Atmospheric Administration (NOAA)) Functional form: Continuous Measurement: DS1923 iButton Hygrochron heat and humidity measurement device
**Indoor thermal comfort**	Definition: Current heat experience measured using heat strain score index. A score of < 13.5 indicates no or low heat strain, between 13.6–18 indicates potential for heat-induced illness, and > 18 indicates the onset of heat-induced illness Functional form: Categorical Measurement: Heat strain score index scale comprising 18 questions answered by individuals at the time of interview
**Systolic blood pressure**	Definition: Systolic blood pressure in mmHg Functional form: Continuous Measurement: Omron portable automated sphygmomanometers
**Diastolic blood pressure**	Definition: Diastolic blood pressure in mmHg Functional form: Continuous Measurement: Omron portable automated sphygmomanometers
**Body temperature**	Definition: Body temperature Functional form: Continuous Measurement: Inner ear thermometer
**Dehydration**	Definition: Loss of fluid greater than intake amount resulting in the body being unable to carry out its normal functions Functional form: Categorical Measurement: Urine hydration chart and question answered by individual
**Blood glucose (HbA1c)**	Definition: Average blood glucose measured over 3 months Functional form: Continuous Measurement: HemoCue® HbA1c 501 System to capture estimated average glucose (g/L)
**Sleep**	Definition: Number of hours slept and number of times the individual woke up Functional form: Count Measurement: Recall question answered by individual and smartwatch (in a subset of the cRCT population)
**Cognition**	Definition: The mental processes involved in gaining knowledge and comprehension Functional form: Continuous Measurement: Oxford Cognitive Screen (OCS)-Plus (assessing memory, language, visual-spatial ability, and executive functioning domains)

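### The 2 SD 'anomaly' rule for indoor climate readings flags genuine heat, mainly in control homes if the roof works, and the plan does not say what happens to flagged readings

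*Protocol article*

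**What the plan says.** The rule stands in the protocol article under Analysis of smartwatch data. Indoor and outdoor temperature and humidity, "collected in 15-min intervals, will be averaged at the hourly level", are screened as follows: "We will categorize environmental data as anomalies when measurements are two standard deviations beyond the corresponding monthly average values based on roof type". The two roof types are mud brick and tin. Neither hour of day nor trial arm is named as a stratum. The text does not say whether screening comes before or after hourly averaging, or what follows from the label.

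For heart rate the next paragraph is explicit: "we will exclude duplicate heart rate measurements or those that exceed the age-predicted maximum heart rate as implausible values". Overlapping or very short sleep records are also dropped outright.

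Air temperature is a secondary endpoint in Table 2 ("Definition: Ambient air temperature", in °C), measured with the iButton logger. Relative humidity and heat index come from the same device. Temperature is also the exposure in the smartwatch heart-rate and sleep models. Under Intervention, homes of each roof type are randomized 1:1.

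**The concern.** An anomaly rule should find readings that the instrument got wrong. This one finds readings far from a monthly mean. Even fault-free, normally distributed data would have about 5% of values beyond two SD. Indoor temperature also has a daily cycle, so the upper tail consists largely of hot afternoons. Cooling the house in the daytime is what the intervention is meant to do, so a working roof takes intervention homes out of that tail and leaves control homes in it. The flag then depends on the outcome and differs by arm.

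Whether harm follows depends on the next step, which is not stated. If flagged values are set aside as errors, the comparison loses control-arm heat that the roof is supposed to prevent. The smartwatch models also lose the hot end of their exposure range.

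**Working it through.** **No figure to reproduce.** The article gives no share flagged, no indoor SD and no bias for this rule, so its behaviour was simulated.

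**Inputs from the article**
- Table 1 (outdoor): mean daily minimum 23.1, average 29.6, maximum 36.1 °C. Half-range = (36.1 − 23.1)/2 = 6.5 °C. The highest daily maximum is 43.9 °C.
- Cooling: studies from India are said to "reduce daytime indoor air temperature by approximately" 2.5 °C; Power calculations speaks of 3–4 °C.
- Both arms in equal numbers within roof type.

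**Assumptions not in the article**
- One month and one roof type: 150 homes per arm × 30 days × 24 h, 40 replicates.
- Daily profile sinusoidal or midday-peaked; half-range 3 °C (damped indoors) or 6.5 °C.
- Day-to-day SD 1 or 2 °C, between-home SD 1 °C, 15% variation in amplitude between homes, sensor noise 0.3 °C.
- Peak daytime cooling 0, 1, 2.5 or 4 °C with none at night, or 2.5 °C at all hours.
- No sensor faults, so every flag falls on a genuine reading. Cut at mean ± 2 SD over all hours and both arms.

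**Where the cut falls.** For a pure sinusoid of amplitude A, SD = A/√2, so 2 SD = 1.41A. An average afternoon is therefore not flagged, only hotter days or homes. Take the sinusoid with half-range 6.5, day SD 1 and 2.5 °C daytime cooling (24-h mean effect 0.73 °C):
- Pooled mean = 29.6 − 0.73/2 = 29.24; pooled SD = 4.53; upper cut = 29.24 + 2 × 4.53 = 38.3 °C.
- Average control peak = 29.6 + 6.5 = 36.1, so a control home needs 38.3 − 36.1 = 2.2 °C extra to be flagged.
- Average intervention peak = 36.1 − 2.5 = 33.6, so an intervention home needs 38.3 − 33.6 = 4.7 °C extra.

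That gap is the source of the imbalance.

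**Selected results** (2.5 °C cooling, day SD 1). Loss = 1 − after/before when flagged readings are dropped.

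| Profile, half-range, cooling | High flags, control / intervention | Low flags, control / intervention | 24-h effect (°C) | 12–17 h effect (°C) |
|---|---|---|---|---|
| Sinusoid, 6.5, daytime | 1.35% / 0.07% | 0.54% / 0.54% | 0.73→0.61 (16%) | 2.14→1.95 (9%) |
| Sinusoid, 6.5, all hours | 1.24% / 0.03% | 0.03% / 1.24% | 2.50→2.27 (9%) | 2.50→2.32 (7%) |
| Peaked, 3, daytime | 7.51% / 0.59% | 0.57% / 0.58% | 0.73→0.33 (55%) | 2.14→1.41 (34%) |
| Peaked, 6.5, daytime | 6.41% / 1.03% | 0.00% / 0.00% | 0.73→0.13 (83%) | 2.14→1.23 (42%) |
| Peaked, 6.5, all hours | 5.59% / 0.76% | 0.00% / 0.02% | 2.50→1.97 (21%) | 2.50→1.68 (33%) |

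Percentages come from unrounded values.

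- First row, control share of high flags: 1.35/(1.35 + 0.07) = 95%. Of all flags: (1.35 + 0.54)/(1.35 + 0.07 + 0.54 + 0.54) = 1.89/2.50 = 76%.
- Second row, control share of all flags: (1.24 + 0.03)/(1.24 + 0.03 + 0.03 + 1.24) = 50%. The effect still shrinks, because the low flags fall in intervention homes.

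**All scenarios with cooling**
- High flags: 68–99% fall at 12–17 h and 63–99% are in control homes.
- All flags: control share 50–95%.
- Loss of the 24-h effect: 9–27% (sinusoid); 16–86% (peaked). Within the peaked profile: 16–21% with all-hours cooling, 37–62% with daytime cooling and half-range 3, and 68–86% with daytime cooling and half-range 6.5.
- Loss of the 12–17 h effect: 7–21% (sinusoid); 25–43% (peaked).

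**Controls.** With no cooling, flags split 50:50 and no bias appears. With flagged readings kept, the effect is unchanged. Limits set within hour and arm, run only as a contrast, also left it unchanged (0.73→0.73 °C).

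**The case against.** The strongest reply is that the article never says flagged readings are removed. It uses a verb of labelling here and verbs of exclusion for heart rate and sleep in the same section, and handling may be settled in a fuller document. This stands: a reader might infer that the plan trims control-home heat, and the text does not support that as fact. The rule as worded is still a poor definition of an anomaly. It sits among cleaning steps, and no other use for the label is given.

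Pooling over arms and hours is likewise inferred from the strata named. It is the plainer reading, not a stated one.

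A reader might also infer that most flags of any kind come from control homes. The rule is two-sided, and under uniform cooling flags split evenly; the statement holds for high readings.

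Nor can one say that the loss is worst in the hottest month. The cut is month-specific, so April is judged against April, and only a generic month was simulated. Humidity and heat index were not simulated.

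The simulation gave the rule no chance to help, since it contained no faults. The Timeline section reports early equipment malfunctions, though it does not name the device.

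Finally, the rule is placed under the smartwatch analysis. It is the only screening rule given for environmental data, but the article does not say outright that it governs the temperature endpoint.

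**Conclusion.** The point holds conditionally. As worded, the rule labels genuine heat as anomalous, and if the roof cools, the high labels fall mainly on control homes. Labelling alone causes no bias. Removal under limits pooled over arms and hours shrank the temperature effect in every scenario with cooling: roughly 10–25% of the 24-h mean effect for a smooth day, and well over half for a sharply peaked day with daytime-only cooling. No single figure should be taken as the likely size, because the article gives neither an indoor profile nor an indoor SD.

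The consequence is limited to the indoor temperature endpoint, which is secondary, and the exposure range in the smartwatch models. The monthly heart-rate comparison by arm does not use these readings. The rule should be corrected, but it does not threaten the primary analysis.

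**What to change.** Rewrite the cleaning rule in three parts.

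1. Define an anomaly by instrument faults that depend on neither arm nor heat: a value outside the sensor's range, a stuck value, an impossible jump between consecutive 15-minute readings, or a logger removed from the home.
2. State that every physically possible reading stays in the main analysis, both for the environmental endpoints and for the temperature exposure in the smartwatch models.
3. Keep the 2 SD rule only as a sensitivity analysis. State its reference set, and report counts of high and low flags by arm.

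No new data are needed. The cost is a rewritten rule, and a few faulty readings that look physically possible may remain.
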